## Safety reporting

In Japan, the principal investigator will provide documentation of all SAEs to the Director of the investigative site and the Sponsor.

## Clinical Expense and Compensation:

### *Expenditure of the Clinical Expense*

The Sponsor will pay the expenses related to this study to the investigative site in accordance with "Special Healthcare Expenditure." The expenses of screening test, etc., will be paid based on the contract concluded with each investigative site. To lighten the burden imposed on the subject with participation to the study, transportation expenses, etc., will be paid to the subjects via participating investigative site in accordance with the rules of the investigative site.

### *Compensation for Health Impairment and Insurance*

1. If a subject suffers some sort of health impairment due to this study, the investigative site will provide treatment and take other necessary measures. Among the expenses required for the treatment, the amount not covered by health insurance that the subject must pay directly will be borne by the Sponsor only when the event is associated with the use of the study drug.
2. When a subject suffers health impairment during this study and a dispute occurs or might occur between the investigative site and the subject, the investigative site will report it to the Sponsors immediately and resolve it. The Sponsor will cooperate with the investigative site in resolving the problem.
3. When the investigative site must compensate to the subject's health impairment caused by this study, the compensation paid by the investigative site and the expenses related to any dispute will be borne in full by the Sponsor, except in cases where the responsibility for the problem is attributed to the investigative site. This shall not apply to cases where the health impairment occurred because the investigative site performed the study with marked deviation from the GCP or the protocol or because of a deliberate action or a major error by the investigative site.
4. When a subject suffers health impairment during this study and liability for compensation arises, the Sponsor will compensate in accordance with the standard operating procedure regarding the compensation prepared in advance.
5. The Sponsor will obtain clinical study insurance and will take other necessary measures to cover the claims and compensation required in such cases.

## Consent

Written consent is necessary both from the subject and his/her legal representative if he/she is under the age of 20 years.

If a Japanese subject under the age of 20 years has reached 20 years while participating in the study, new written consent is necessary from the subject regarding continued participation in the study.

## Confinement

In Japan, the subjects in Dose Escalation will be hospitalized during the DLT evaluation period for the purpose of safety management.

## Protocol Deviations

Investigators must record all protocol deviations in the appropriate medical records. The principal investigator must report protocol deviations which were necessary to eliminate an immediate hazard to

study subjects, attaching the reasons for protocol deviations, to both AbbVie and the head of medical institution.

### Contraception

- Combined (estrogen and progestogen containing) hormonal birth control (oral, intravaginal,\* transdermal,\* injectable) associated with inhibition of ovulation initiated at least 1 month prior to study Baseline Day 1.
- Progestogen-only hormonal birth control (oral, injectable,\* implantable\*) associated with inhibition of ovulation initiated at least 1 month prior to study Baseline Day 1.

\* Not approved in Japan.

## 5.2 SUSAR Reporting

---

AbbVie will be responsible for SUSAR reporting for the IMP in accordance with global and local guidelines and Appendix A of the Investigator Brochure will serve as the Reference Safety Information (RSI). The RSI in effect at the start of a DSUR reporting period serves as the RSI during the reporting period. For follow-up reports, the RSI in place at the time of occurrence of the 'suspected' Serious Adverse Reaction will be used to assess expectedness.

## 6 STUDY DRUG

### 6.1 Treatments Administered

---

ABBV-467 will be administered as an IV infusion once weekly for each 28-day cycle over at least a 30-minute period, as listed in Section 2.1. Various doses will be administered, as determined by dose-escalation rules. ABBV-467 will be provided by AbbVie as a solution in a glass vial. The vial will contain [REDACTED] of ABBV-467 (refer to Protocol Section 5.7 for study drug information). After preparation of the dose for infusion and during infusion, the solution must be protected from exposure to light.

Study drug must not be dispensed without contacting the IRT system. Study drug may only be dispensed to subjects enrolled in the study through the IRT system. At the end of the Treatment Period or at the Final Visit, the site will contact the IRT system to provide visit date information and study drug return information for each kit.

### 6.2 Packaging and Labeling

---

ABBV-467 will be packaged in vials with quantities sufficient to accommodate study design. Each kit will be labeled per local requirements and this label must remain affixed to the kit. All blank spaces on the labels should be completed by site staff prior to dispensing to subject.

#### Storage and Disposition of Study Drug

ABBV-467 must be shipped and stored at controlled temperature (–25° to –10°C) and protected from light.

The investigational products are for investigational use only and are to be used only within the context of this study. The study drug supplied for this study must be maintained under adequate security and stored under the conditions specified on the label until dispensed for subject use or destroyed on site as appropriate.

## 6.3 Method of Assigning Subjects to Treatment Groups

---

This is an open-label, dose-escalation and dose-expansion study. At the screening visit, all subjects will be assigned a unique identification number through the use of the IRT system. For subjects who do not meet the study selection criteria, the site personnel must contact the IRT system and identify the subject as a screen failure.

Subjects who are enrolled will retain their identification number assigned at the screening visit throughout the study. Upon receipt of study drug, the site will acknowledge receipt in the IRT system.

Contact information and user guidelines for IRT use will be provided to each site.

## 6.4 Selection and Timing of Dose for Each Subject

---

Selection of the doses for this study is discussed in Protocol Section 4.2. All subjects should take all doses of study medications as detailed in Section 6.1. ABBV-467 will be administered on the designated study days as specified in Section 2.1. The study drug information is provided in Protocol Section 5.7.

## 6.5 Preparation/Reconstitution of Dosage Form

---

Written instructions for the preparation of ABBV-467 solutions for infusion will be provided as a separate document from the protocol.

## 7 Appendices

### 7.1 HEPATITIS B VIRUS TESTING GUIDELINES FOR ELIGIBILITY

[figure not shown]

DNA= deoxyribonucleic acid; HBc Ab= hepatitis core antibody; HBs Ab = hepatitis B surface antibody; HBs Ag = hepatitis B surface antigen; HBV = hepatitis B virus; PCR = polymerase chain reaction

\* A positive test result for HBs Ab is expected for subjects who have had an HBV vaccination. For subjects without a history of HBV vaccination (and where mandated by local requirements), a positive result for HBs Ab requires HBV DNA PCR testing.

## 7.2 NATIONAL COMPREHENSIVE CANCER NETWORK RISK CATEGORIZATION: GUIDELINES FOR AML (Version 1.2019)

| Risk Category     | Cytogenetics                                                                                                                                        |
|-------------------|-----------------------------------------------------------------------------------------------------------------------------------------------------|
| Favorable Risk    | Core binding factor: inv(16) or t(16;16) or t(8;21)
t(15;17)                                                                                     |
| Intermediate Risk | Normal cytogenetics
+8 alone
t(9;11)
Other non-defined                                                                                     |
| Poor Risk         | Complex (≥ 3 clonal chromosomal abnormalities)
Monosomal karyotype
-5,5q-, -7,7q-
11q23-non t(9;11)
inv(3), t(3;3)
t(6;9)
t(9;22) |

## 7.3 INTERNATIONAL MYELOMA WORKING GROUP RESPONSE CRITERIA

| Category                          | IMWG Response Criteria a                                                                                                                                                                                                                                                                                                                                                                                                                                                                                                                                                                                                                                                                                                                                                   |
|-----------------------------------|---------------------------------------------------------------------------------------------------------------------------------------------------------------------------------------------------------------------------------------------------------------------------------------------------------------------------------------------------------------------------------------------------------------------------------------------------------------------------------------------------------------------------------------------------------------------------------------------------------------------------------------------------------------------------------------------------------------------------------------------------------------------------------------|
| Stringent complete response (sCR) | 
Complete response as defined below, plus the following:
 
 
• Normal FLC ratio
 
• Absence of clonal cells in bone marrow by immunohistochemistryb
 
                                                                                                                                                                                                                                                                                                                                                                                                                                                                                                                                                             |
| Complete response (CR)            | 
 
• Negative immunofixation on the serum and urine
 
• < 5% plasma cells in bone marrow aspirates
 
• Disappearance of any soft tissue plasmacytomas
 
                                                                                                                                                                                                                                                                                                                                                                                                                                                                                                                                                                 |
| Very good partial response (VGPR) | 
 
• Serum and urine M-protein detectable by immunofixation but not on electrophoresis, or
 
• ≥ 90% reduction in serum M-protein plus urine M-protein level < 100 mg per 24 hours
 
                                                                                                                                                                                                                                                                                                                                                                                                                                                                                                                                           |
| Partial response (PR)             | 
 
• ≥ 50% reduction of serum M-protein plus reduction in 24 hours urinary M-protein by ≥ 90% or to < 200 mg per 24 hours.
 
• If the serum and urine M-protein are not measurable, a ≥ 50% decrease in the difference between involved and uninvolved FLC levels is required in place of the M-protein criteria.
 
• If serum and urine M-protein are not measurable, and serum-free light assay is also not measurable, ≥ 50% reduction in plasma cells is required in place of M-protein, provided baseline bone marrow plasma-cell percentage was ≥ 30%.
 
• In addition to the above criteria, if present at baseline, a ≥ 50% reduction in the size (SPD) of soft tissue plasmacytomas is also required.
 
 |
| Minimal response (MR)             | 
 
• ≥ 25% but ≤ 49% reduction of serum M-protein and reduction in 24-hour urine M-protein by 50% to 89%.
 
• In addition to the above listed criteria, if present at baseline, a ≥ 50% reduction in the size (SPD) of soft tissue plasmacytomas is also required.
 
                                                                                                                                                                                                                                                                                                                                                                                                                                                              |
| Stable disease (SD)               | 
 
• Not meeting criteria for CR, VGPR, PR, MR, or progressive disease
 
                                                                                                                                                                                                                                                                                                                                                                                                                                                                                                                                                                                                                                                                 |

| Category                                                             | IMWG Response Criteria a                                                                                                                                                                                                                                                                                                                                                                                                                                                                                                                                                                                                                                                                                                                                                                                                                                                                                                                                                                                                                                                                                                                                                                                                                                                                                                                                                                               |
|----------------------------------------------------------------------|-------------------------------------------------------------------------------------------------------------------------------------------------------------------------------------------------------------------------------------------------------------------------------------------------------------------------------------------------------------------------------------------------------------------------------------------------------------------------------------------------------------------------------------------------------------------------------------------------------------------------------------------------------------------------------------------------------------------------------------------------------------------------------------------------------------------------------------------------------------------------------------------------------------------------------------------------------------------------------------------------------------------------------------------------------------------------------------------------------------------------------------------------------------------------------------------------------------------------------------------------------------------------------------------------------------------------------------------------------------------------------------------------------------------|
| Progressive disease c                                     | 
Any 1 or more of the following criteria:
 
 
• Increase of 25% from lowest confirmed response value in 1 or more of the following criteria:d 
 
• Serum M-protein (absolute increase must be <math>\geq 0.5</math> g/dL);
 
• Serum M-protein increase <math>\geq 1</math> g/dL, if the lowest M component was <math>\geq 5</math> g/dL;
 
• Urine M-protein (absolute increase must be <math>\geq 200</math> mg/24 hours);
 
• In subjects without measurable serum and urine M-protein levels, the difference between involved and uninvolved FLC levels (absolute increase must be <math>> 10</math> mg/dL);
 
• In subjects without measurable serum and urine M-protein levels and without measurable involved FLC levels, bone marrow plasma-cell percentage irrespective of baseline status (absolute increase must be <math>\geq 10\%</math>);
 
 
 
• Appearance of a new lesion(s), <math>\geq 50\%</math> increase from nadir in SPD of <math>> 1</math> lesion, or <math>\geq 50\%</math> increase in the longest diameter of a previous lesion <math>> 1</math> cm in short axis;
 
• <math>\geq 50\%</math> increase in circulating plasma cells (minimum of 200 cells per <math>\mu</math>L) if this is the only measure of disease
 
 |
| Clinical Relapse                                                     | 
 
• Clinical relapse requires 1 or more of the following criteria: 
 
• Direct indicators of increasing disease and/or end organ dysfunction (CRAB features) related to the underlying clonal plasma-cell proliferative disorder;
 
• Development of new soft tissue plasmacytomas or bone lesions (osteoporotic fractures do not constitute progression);
 
• Definite increase in the size of existing plasmacytomas or bone lesions. A definite increase is defined as a 50% (and <math>\geq 1</math> cm) increase as measured serially by the SPD of the measurable lesion;
 
• Hypercalcemia (<math>> 11</math> mg/dL);
 
• Decrease in hemoglobin of <math>\geq 2</math> g/dL not related to therapy or other non-myeloma-related conditions;
 
• Rise in serum creatinine by 2 mg/dL or more from the start of the therapy and attributable to myeloma;
 
• Hyperviscosity related to serum paraprotein
 
 
 
                                                                                                                                                                                                                                                                                                                                                       |
| MRD Criteria (requires a complete response, as defined above) |                                                                                                                                                                                                                                                                                                                                                                                                                                                                                                                                                                                                                                                                                                                                                                                                                                                                                                                                                                                                                                                                                                                                                                                                                                                                                                                                                                                                                   |
| Sustained MRD-negative                                               | MRD negativity in the marrow (NGF or NGS, or both) and by imaging, confirmed minimum of 1 year apart. Subsequent evaluations can be used to further specify the duration of negativity (e.g., MRD-negative at 5 years) e                                                                                                                                                                                                                                                                                                                                                                                                                                                                                                                                                                                                                                                                                                                                                                                                                                                                                                                                                                                                                                                                                                                                                                               |
| Flow MRD-negative                                                    | Absence of phenotypically aberrant clonal plasma cells by NGF f on bone marrow aspirates using the EuroFlow standard operation procedure for MRD detection in multiple myeloma (or validated equivalent method) with a minimum sensitivity of 1 in $10^5$ nucleated cells or higher                                                                                                                                                                                                                                                                                                                                                                                                                                                                                                                                                                                                                                                                                                                                                                                                                                                                                                                                                                                                                                                                                                                    |

| Category                  | IMWG Response Criteria a                                                                                                                                                                                                                                                                                                                              |
|---------------------------|------------------------------------------------------------------------------------------------------------------------------------------------------------------------------------------------------------------------------------------------------------------------------------------------------------------------------------------------------------------|
| Sequencing MRD-negative   | Absence of clonal plasma cells by NGS on bone marrow aspirate in which presence of a clone is defined as less than 2 identical sequencing reads obtained after DNA sequencing of bone marrow aspirates using the LymphoSIGHT platform (or validated equivalent method) with a minimum sensitivity of 1 in 10  nucleated cells g or higher |
| Imaging plus MRD-negative | MRD negativity as defined by NGF or NGS plus disappearance of every area of increased tracer uptake found at baseline or a preceding PET/CT or decrease to less mediastinal blood pool SUV or decrease to less than that of surrounding normal tissue h                                                                                               |

CRAB features = calcium elevation, renal failure, anemia, lytic bone lesions; FLC = free light chain; IHC = immunohistochemistry; M-protein = myeloma protein; MFC = multiparametric flow cytometry; MRD = minimum residual disease; NGF = next generation flow; NGS = next generation sequencing; SPD = sum of the products of the maximal perpendicular diameters of measured lesions

Adapted from Kumar et al, 2016

- All response categories require 2 consecutive assessments made at any time before the initiation of any new therapy; All categories of response and MRD also require no known evidence of progressive or new bone lesions if radiographic studies were performed. Radiographic studies are not required to satisfy these response requirements, except for the requirement of FDG PET if imaging MRD-negative status is reported. Bone marrow assessments need not be confirmed.
- Presence/absence of clonal cells is based upon the  $\kappa/\lambda$  ratio. An abnormal  $\kappa/\lambda$  ratio by IHC requires a minimum of 100 plasma cells for analysis. An abnormal ratio reflecting presence of an abnormal clone is  $\kappa/\lambda$  of  $> 4:1$  or  $< 1:2$ .
- Positive immunofixation alone in a subject previously classified as achieving a complete response will not be considered progression.
- In the case where a value is felt to be a spurious result per physician discretion (for example, a possible laboratory error), the value will not be considered when determining the lowest value.
- Sustained MRD negativity when reported should also annotate the method used (for example, sustained flow MRD negative, sustained sequencing MRD negative).
- Bone marrow MFC should follow NGF guidelines.
- DNA sequencing assay on bone marrow aspirate should use a validated assay such as LymphoSIGHT (Sequentia).
- Imaging should be performed once MRD negativity is determined by MFC or NGS following criteria used by Zamagni, et al.

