#### Multiple Myeloma

For MM, efficacy will be evaluated per adapted International Myeloma Working Group (IMWG) criteria:

- Overall response rate (ORR), defined as partial response (PR) + very good partial response (VGPR) + complete remission (CR) + stringent complete response (sCR).
- Clinical benefit rate (CBR), defined as minimal response (MR) + PR + VGPR + CR + sCR.

Duration of response (DOR), defined as the time between date of first response and the first occurrence of progression or death from any cause, whichever occurs first.

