### Plasmacytoma Evaluation

CT, MRI, or PET-CT scans should be performed at baseline, if clinically indicated, to assess for presence of extramedullary plasmacytoma. Plasmacytoma evaluation should be performed to confirm PR/CR or progressive disease, or otherwise as clinically indicated, every 12 - 16 weeks. The same radiological method should be used throughout the study.

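### Operations Manual 7.3 gives VGPR no plasmacytoma condition, so a subject with VGPR-depth M-protein who fails PR only on a persisting plasmacytoma still counts as a responder

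*Protocol*

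**What the plan says.** The response table in Operations Manual 7.3 (Appendix J) treats soft-tissue plasmacytomas as follows.

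- **CR:** "Disappearance of any soft tissue plasmacytomas".
- **VGPR:** two alternative routes, both on M-protein. The first is "Serum and urine M-protein detectable by immunofixation but not on electrophoresis, or"; the second is at least a "90% reduction in serum M-protein plus urine M-protein level" below 100 mg per 24 hours. Neither mentions plasmacytomas.
- **PR:** after the M-protein rules, "In addition to the above criteria, if present at baseline", at least a 50% "reduction in the size (SPD) of soft tissue plasmacytomas is also required".
- **MR:** the same lesion condition, introduced by "In addition to the above listed criteria, if present at baseline".
- **Stable disease:** the residual category, open only to subjects who meet none of CR, VGPR, PR, MR or progression.

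Only stringent CR is built on another category (CR plus further conditions). VGPR is not written as PR plus something.

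On imaging, Operations Manual 3.16 says: "Plasmacytoma evaluation should be performed to confirm PR/CR or progressive disease". It then also allows evaluation when clinically indicated, every 12 to 16 weeks. The note to the Day 1 visits in Operations Manual 2.1 is to the same effect. Neither names VGPR.

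Protocol 3.2 defines myeloma ORR as the sum of PR, VGPR, CR and stringent CR, and CBR as those plus MR. Protocol 7.3 analyses DOR among subjects who reached PR or better, VGPR included.

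**The concern.** The categories are read as a ladder, with a deeper response at least as demanding as a shallower one in every respect. On the plasmacytoma this table breaks that order: the condition applies at MR and PR, is absent at VGPR, and returns in stricter form at CR. A lesion that blocks the shallower response does not block the deeper one.

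At stake is what Part B reports. ORR, CBR and DOR could include subjects whose extramedullary disease did not respond. The misclassification can only add responders. The protocol does treat such disease as part of response: Section 5.3 removes only resected or irradiated extramedullary sites from later response assessments, which implies that other sites count. Subjects with plasmacytomas are expected (Protocol 6.2 lists bulky plasmacytomas among the tumor lysis risk factors), and the eligibility criteria do not exclude them.

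**Working it through.** **1. Apply the table as written.** Assume immunofixation stays positive (so no CR), M-protein remains visible on electrophoresis (so only the second VGPR route is open), and progression criteria are not met.

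| Serum M-protein | Urine M-protein | Baseline plasmacytoma | VGPR | PR | MR | Category |
|---|---|---|---|---|---|---|
| -95% | -95%, to 50 mg/24 h | unchanged | yes | no | no | VGPR, in ORR |
| -95% | -95%, to 50 mg/24 h | -60% | yes | yes | no | VGPR, in ORR |
| -70% | -95%, to 50 mg/24 h | unchanged | no | no | no | stable disease |
| -40% | -60%, to 150 mg/24 h | unchanged | no | no | no | stable disease |

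In row 1, PR fails only on the lesion. MR fails whatever the lesion does, because its serum band is 25-49%. CR fails on immunofixation. The decisive comparison is therefore VGPR against PR. Rows 1 and 3 have the same lesion and the same urine result; only the depth of the serum fall differs, and the subject moves from stable disease to VGPR.

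**2. Look for a repair elsewhere.**
- Footnote a to the table bars progressive or new bone lesions. It does not reach an unchanged soft-tissue lesion.
- The progression row catches new or sufficiently enlarged lesions, not one that is stable or shrinks by less than 50%.
- Stable disease cannot absorb the subject, because it excludes anyone who meets VGPR.
- Operations Manual 3.16 makes electrophoresis and immunofixation mandatory at a possible VGPR, but its plasmacytoma paragraph omits VGPR.

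No provision closes the gap.

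**3. Size of one reclassification.** First reproduce Protocol Table 5. The exact one-sided 80% lower bound for x responders among n = 20 is the 0.20 quantile of Beta(x, n - x + 1):

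| x | Recomputed | Table 5 |
|---|---|---|
| 5 | 0.1584 | 0.158 |
| 6 | 0.2013 | 0.201 |
| 7 | 0.2454 | 0.245 |
| 8 | 0.2906 | 0.291 |
| 10 | 0.3840 | 0.384 |

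All five agree. One subject is 1/20 = 5 percentage points of ORR, or 1/24 = 4.2 points if all 24 permitted subjects are enrolled. Now remove one responder from the example in Protocol 7.7:

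| | 5/20 | 4/20 |
|---|---|---|
| ORR | 25% | 20% |
| One-sided 80% lower bound | 0.158 | 0.117 |
| Two-sided 90% Clopper-Pearson (Protocol 7.3) | 0.104 to 0.456 | 0.071 to 0.401 |

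The statement in Protocol 7.7 that a 25% observed rate excludes 15% holds at 5/20 (0.158 > 0.15) and fails at 4/20 (0.117 < 0.15).

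**4. How many subjects.** The documents do not give the share with a baseline plasmacytoma. For illustration only, assume 10-30%, which is 2 to 6 of 20. Assume further that 10-20% of those reach VGPR-depth M-protein, and that 20-50% of these have a lesion that does not shrink by half. The expected number misclassified is then 2 × 0.10 × 0.20 = 0.04 to 6 × 0.20 × 0.50 = 0.6 per 20 subjects. All three ranges are assumptions.

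**The case against.** The strongest reply is that the reach is narrow. A misclassified subject needs a baseline plasmacytoma, M-protein of VGPR depth, lesion shrinkage under 50% and no progression, all at once. Efficacy is a secondary, preliminary objective, Protocol 7.7 plans no hypothesis test, and no stated decision rule turns on one responder. All of this stands, and it limits the weight of the point.

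A second reply is that the table is labelled as adapted from published consensus criteria, so the VGPR wording may come from the source. That cannot be settled from the documents. If it does, the fix is a study-specific departure that could reduce comparability with other trials. It does not remove the inconsistency within the table that investigators are told to use, and a table described as adapted is the sponsor's to word.

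A reader might also infer more than the text supports:

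- *That any subject who fails PR on a plasmacytoma becomes a VGPR.* Not so: with a 50-89% serum fall and M-protein still visible on electrophoresis, the result is stable disease.
- *That such a subject fails MR and CR because of the lesion.* A serum fall of 90% or more lies outside the MR band in any case, and CR normally fails on immunofixation.
- *That VGPR is easier to reach than PR.* This is true only of the lesion condition; its M-protein demands are stricter.
- *That plasmacytomas are imaged only to confirm PR, CR or progression.* Operations Manual 3.16 also provides for evaluation as clinically indicated every 12 to 16 weeks. What is missing is a lesion threshold for VGPR and a prompt to evaluate at that point.
- *That 2 to 6 of 20 subjects would be misclassified.* Under the assumed 10-30%, that figure counts subjects with a baseline plasmacytoma, not subjects wrongly called responders.

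**Conclusion.** The point holds in this limited form. VGPR is not nested within PR, and nothing else in the protocol stops a subject with VGPR-depth M-protein and a stable or insufficiently reduced plasmacytoma from counting in ORR, CBR and DOR. Per subject, the effect is 5 points of ORR in a cohort of 20, which is enough at the protocol's own example to lose the exclusion of 15%. The total effect is unknown and probably small: it depends on plasmacytoma prevalence, depth of M-protein response and discordance between the two, none of which the documents give. The harm is to estimation of a secondary endpoint. No conclusion about the direction of any deviation from the source criteria can be drawn. It merits correction because the change is cheap and settles a classification before data arrive; it does not threaten the primary objectives.

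**What to change.** In Operations Manual 7.3, add to the VGPR row that the PR plasmacytoma condition also applies to both routes: where a plasmacytoma was present at baseline, an SPD reduction of at least 50% is needed. In the plasmacytoma paragraph of Operations Manual 3.16 and the Day 1 note in Operations Manual 2.1, change 'PR/CR' to 'PR/VGPR/CR'.

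The costs are modest. ORR may be slightly lower. A VGPR subject with a baseline plasmacytoma needs the follow-up evaluation already called for at PR and CR. If the source criteria carry the current VGPR wording, the change is a study-specific adaptation and should be declared as one, or ORR should also be shown under the unmodified wording so that comparison with other trials remains possible.
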